#### Secondary outcomes

A number of secondary outcomes will be measured, using various instruments.

• The five-item EuroQoL (EQ-5D) is a standardized generic measure of health-related quality of life (HRQOL), which is suitable for use in people with a wide range of health conditions, and is recommended by NICE for economic evaluations in clinical trials. It can be completed by patients, and may be used as a postal questionnaire or in interview [66]. Further, it has proven reliability, validity, and responsiveness in type 2 diabetes, suggesting that it can be used for modeling health outcomes in economic evaluations of interventions for people with type 2 diabetes [67].

• The World Health Organization Quality of Life brief measure (WHOQoL-BREF) is a measure of global QOL, which has been validated in a large international population for a wide range of illnesses [68]. The brief measure is a 26-item version of the 100-item WHOQoL measure. QOL is measured across four domains that have been shown to be salient: physical, psychological, social, and environmental. Items are measured using a five-point Likert-type response; a low score for each item is indicative of poor QOL. Three items are negatively phrased and reverse scored. Scores from each domain are calculated using the mean score for the items within that domain, and multiplying the mean score by four, so that scores taken from the WHOQoL-BREF may be compared and contrasted with the 100-item WHOQoL measure. Additionally, the WHOQoL contains a single-item scale for QOL. The first item on the questionnaire ‘How would you rate your quality of life?’ can be interpreted individually as a measure of patient-reported QOL. Additionally the total score of the WHOQoL has been shown to operate effectively as a unidimensional measure of QOL [69].

• The Diabetes Quality of Life (DQoL) tool measures both the physical and emotional effects of diabetes and diabetes treatment using five scales: satisfaction with treatment; impact of treatment; worry about the future effects of diabetes; worry about social and vocational issues; and overall well-being [70].

• The Seattle Angina Questionnaire (SAQ) is a reliable and predictive tool that measures five clinically important dimensions of functional status in people with coronary artery disease [71].

• The seven-item Generalized Anxiety Disorder (GAD-7) is a self-report scale measuring symptom severity of GAD over the previous 2 weeks on a four-point Likert scale with a cut-off of greater than or equal to 8 [72].

• Self-efficacy: changes in self-efficacy cognitions (that is, a person’s confidence to produce a desired outcome) are theorized to lead directly to changes in self-rated health and thereby influence healthcare utilization. Validated scales used in the evaluation of the Expert Patient Program will be used [73].

• Patient self-management behavior will be evaluated using the Health Education Impact Questionnaire (heiQ). This 42-item scale measures eight independent dimensions, including positive and active engagement in life, health-directed behaviors; skill and technique acquisition; constructive attitudes and approaches; self-monitoring and insight; health-service navigation; social integration and support; and emotional well-being. The heiQ has shown preliminary evidence of construct validity [74].

• The Client Satisfaction Questionnaire (CSQ-8) is an eight-item self-administered questionnaire collected at the end of service delivery and scored using a four-point Likert scale. The CSQ-8 scores range from 8 to 32, with higher values indicating higher satisfaction. Scores are correlated with change in self-reported symptoms as measured by the Client Checklist, a self-report symptom checklist made up of items from the SCL-90. The CSQ-8 gives equivalent results to the CSQ-18, and is shorter and quicker to complete, lending it a practical advantage for use in primary care [75].

• Healthcare utilization will be examined using the Patient Service Utilization questionnaire [29].

• The Patient Assessment of Chronic Illness Care (PACIC-5A) is a patient-centered assessment of implementation of the chronic care model (CCM), which focuses on the receipt of patient-centered care and self-management behavior [76]. In patients with diabetes, the PACIC was shown to be associated with increased exercise and receipt of appropriate laboratory assessments and self-management counseling [77]. PACIC assessments of the implementation of CCM have also been shown to be independently associated with improved self-management behaviors and patient-centered outcomes in adults with a wide range of LTCs, including CHD [78]. The five subscales of the PACIC are patient activation, delivery system/practice design, goal-setting/tailoring, problem-solving/contextual, and follow-up/co-ordination. Six additional items measure minimal contact behavioral counseling interventions provided in primary care, in accordance with the ‘Five As’ construct (assess, advise, agree, assist and arrange) devised by the Canadian Task Force on Preventive Health Care and the US Public Health Service [79,80].

• The ENRICHD Social Support Instrument (ESSI) is a brief seven-item measure of perceived social support[81]. The scale contains six social support items that have been shown to be individually predictive of poor outcome in patients with cardiac disease, and one item that assesses partner status. The scale has acceptable reliability and validity.

• The Sheehan Disability Scale [82] is a brief measure of disability in carrying out life activities across the three domains of work, social, and family life.

• The Relationship Scales Questionnaire (RSQ) is a measure of attachment styles containing 30 short statements describing interpersonal characteristics in close relationships to be rated on five-point Likert scale. Each statement contributes to secure, dismissing, preoccupied, or fearful attachment patterns. Scores for each attachment pattern are derived by taking the mean of items representing each attachment prototype [83].

Where no validated and translated version exists for use with South Asian patients who do not speak English, we will culturally adapt and translate all outcome assessments [84]. The trial will employ a South Asian language specialist who will have responsibility for supporting data collection from Urdu, Bengali, and Gujarati speakers.

### Process evaluation

In addition to primary and secondary outcome measures, we will include measures of characteristics and processes that may predict whether depression and medical outcomes improve within particular groups of patients. Evaluation of predictors of treatment response will include quantitative assessment of the following.

• Patient demographic characteristics, including age, gender, ethnicity, and socioeconomic status. These will be derived from the items used in the General Practice Assessment Questionnaire [85].

• Patient clinical characteristics, including number, type, and burden of LTCs assessed by a self-reported measure of disease burden [86].

• Illness representations, using a modified version of the Brief Illness Perceptions Questionnaire [87], for use in people with multiple morbidities.

• Adherence to treatment intervention with PWP (from contact sheet completed by primary-care practitioner).

• Contextual practice variables: anti-depressant prescription rates, and availability and referral to other mental-health services.

### Measure of contamination

It is possible that PWPs trained by CLAHRC might share knowledge and training about collaborative care with colleagues not enrolled in the COINCIDE trial, thereby subverting the study protocol and threatening the internal validity of the study. However, non-CLAHRC trained PWPs will not be using collaborative care for the duration of the trial when they encounter patients with depression and diabetes/CHD. Thus, the effects of contamination caused by knowledge sharing between PWPs are likely to be minimal. We will measure the effect of contamination between CLAHRC-trained and non-CLAHRC-trained PWPs by assessing changes in knowledge, attitudes, and clinical practice between baseline and follow-up, using previously validated approaches to evaluate depression training programs [88].

The schedule of assessments is shown in Table 2.

**Table 2 T2:** Schedule of assessments

**Patient assessments**	**Time point**		
	**Screening**	**Baseline**	**6 months**
PHQ-9	X	X	X
Demographic variables, past medical and psychiatric history		X	
Current physical illness details (including medication)		X	
Number and burden of diseases		X	
RSQ		X	
Self-efficacy measure		X	X
SCL-90 depression		X	X
EQ-5D		X	X
GAD-7		X	X
DQoL		X	X
SAQ		X	X
WHOQoL-BREF		X	X
heiQ		X	X
ESSI		X	X
AIPQ		X	X
SDS		X	X
Anti-depressant prescription rate and referral to other MHS			X
Healthcare utilization (purpose-designed questionnaire)			X
PACIC			X
CSQ			X
Practitioner assessment			
Change in KAP		X	X

Abbreviations: AIPQ, Adapted Illness Perceptions Questionnaire; CSQ, Client Satisfaction Questionnaire; DQoL, Diabetes Quality of Life; ESSI, Enhancing Recovery in Coronary Heart Disease (ENRICHD) Social Support Instrument; EQ-5D, the five-domain EuroQoL quality of life questionnaire; GAD-7, the seven-item Generalized Anxiety Disorder questionnaire; heiQ, Health Education Impact Questionnaire; KAP, Change in Knowledge, Attitudes, Practice; MHS, mental-health service; PACIC, Patient Assessment of Chronic Illness Care; PHQ-9, the nine-item Patient Health Questionnaire; RSQ, Relationship Scales Questionnaire; SAQ, Seattle Angina Questionnaire; SCL-90, the 90-item Symptoms Checklist; SDS, The Sheehan Disability Scale; WHOQoL-BREF, World Health Organization Quality of Life brief measure.

#### Qualitative process evaluation

Although a considerable evidence base exists for the role of collaborative care in improving treatment of depression [89], there is a recognized gap between the efficacy demonstrated in trials and the implementation of the intervention in everyday practice [28], with particular uncertainty around whether the model will effectively translate to UK healthcare systems [36]. The UK Medical Research Council has highlighted the need for process evaluations to understand the problems of integrating interventions into healthcare settings. Gask *et al*. [89], in an evaluation of collaborative care for depression in primary care in the UK, demonstrated the utility of post-trial interviews of participants, which can provide additional insight beyond pre-trial expectations of performance.

We will therefore undertake a separate qualitative process evaluation to evaluate the extent to which the collaborative-care model was implemented in the intervention GP practices and IAPT teams. The aims of this arm of the process evaluation are to explore: the feasibility and acceptability of collaborative care as experienced by both patients and professionals, with a particular focus on integration of physical and mental health care; the sustainability of collaborative-care models beyond the trial; and the feasibility and acceptability of implementation.

### Professional experiences of delivering collaborative care for depression in long-term conditions

Role congruence, perceived patient acceptability, belief about patients’ capabilities, and perceived effectiveness can all have an effect on the attitudes of primary-care clinicians to treatments and screening [90]. In particular, we will explore whether collaborative care affects the attitudes of professionals toward addressing the physical and mental healthcare needs of people with LTCs in more integrated ways. Gunn *et al*. [91] reported that in their study of depression in primary care, GPs were either ‘integrators’ or ‘separators’. Integrators saw physical and mental health as intrinsically linked, whereas separators tended to deal with physical and mental health problems as distinct. This proposed study will examine whether PWPs trained specifically to address depression in LTCs are able to achieve an integrated approach, and whether they perceive the views of patients and other primary care professionals as congruent with this.

### Patient experience of collaborative care for depression in long-term conditions

Patients’ views about their perceptions of integrated services and also the integration of their physical and mental health care will also be explored. Evidence suggests that the professional background of the case manager is key to the success of collaborative care [24], but it is uncertain whether this is in part associated with patient perceptions and expectations about the role of mental-health professionals compared with physical health specialists such as practice nurses. Patient perceptions and observations about the degree of interaction and integration between professionals will also be explored; for example, whether patients perceive that communication between professionals improved, and whether they report that their conditions were managed in more integrated ways through shared determination of treatment goals or by using interventions that address both physical and mental health problems.

### Sustainability beyond the trial

Although collaborative care has been shown to be effective in managing depression, concerns have been raised about how these effects endure beyond the research context [32]. The process evaluation will explore how successfully the collaborative-care model can be embedded within NHS primary care, where psychological therapy services are provided by usual care providers. For example, we will capture provider and user perspectives to address whether GP practices and existing IAPT services have the capacity to continue working collaboratively, and whether PWPs are the most appropriate professional to train as case managers.

The process evaluation will therefore provide data on both the experience of implementation in practice and the resulting perceptions about the likelihood of the model being integrated in routine practice. These aims will be met through semi-structured interviews, which will be analyzed using normalization process theory (NPT).

### Theoretical model: normalization process theory

Process evaluations are rarely guided by theoretical models, and tend to adopt procedural rather than conceptual approaches to intervention complexity [92]. Theoretical models are necessary to understand and predict problems of integration into practice [92]. This is particularly important for addressing the execution and realization of interventions in a pre-existing operational context such as healthcare settings, where novel interventions must fit into deeply embedded professional and organizational systems.

NPT will be used to develop the topic guides for interviews and provide the framework for analysis. NPT is explicitly concerned with the workability and sustainability of complex interventions, focusing on the routinization of intervention components. NPT asks to what extent novel interventions can be assimilated and embedded into routine practice, making it very consistent with the aim of CLAHRC to identify how interventions can be effectively adopted into actual practice. NPT can therefore be used to address both feasibility of implementation, by recognizing which components of implementation may pose particular barriers, and the likelihood of sustainability, by examining the extent to which the intervention can become integrated within everyday practice.

NPT has been successfully used to guide evaluations of implementation of depression care in healthcare settings [89,91], but has to date not been used to examine embedding of depression interventions for patients with chronic illness. NPT states that implementation can be understood through four generative mechanisms:

• Coherence: the meaning of the practice to actors

• Cognitive participation: engagement, individually and collectively, with the practice

• Collective action: interaction with pre-existing or established processes

• Reflexive monitoring: how the practice is assessed and understood by the actors.

These constructs will be used to guide the analysis of qualitative data from both patients and professionals experiencing the intervention.

### Health economics analysis

The objective of the economic study will be to assess the relative cost-effectiveness of the training intervention to improve patient outcomes and/or the costs of health and social care. The framework of cost-effectiveness and the cost-effectiveness acceptability analysis will be used. The perspective of the study will include the viewpoints of health and social care service providers and patients. These are thought to be the key actors and thus approximate a societal perspective. Costs and outcomes will be discounted at the rate recommended by the UK Treasury at the time of analysis (currently 3.5%).

#### Outcome measures

The primary outcomes of the economic evaluation will be the incremental cost-effectiveness ratio (ICER) and the associated net benefit statistic and probability of cost-effectiveness derived from the cost-effectiveness acceptability analysis. The measure of patient outcome for the economic analysis will be quality-adjusted life years (QALYs) gained at the end of scheduled follow-up. The QALYs will be estimated as the length of time from baseline to end of follow-up, multiplied by the utility of that period. The utility values of the participants will be estimated from the EQ-5D health status questionnaire [66] completed at baseline and follow-up assessments, and the associated published societal utility tariffs.

#### Costs

The direct costs will include the costs of the training intervention and the costs of health and social care services used from recruitment to the end of the scheduled follow-up. The direct costs of treatment and subsequent care will be estimated by summing the costs of each resource used as an input to provide health and social care. For each type of resource, the cost will be estimated as the quantity of that resource used multiplied by the unit cost specific to that resource. In addition, previous health and social care costs are known determinants of future costs. Information will be collected from participants and primary-care records about service use for the 6 months prior to baseline, and these costs will be used as a covariate in the economic data analysis.

The analysis of economic data will use an intent-to-treat approach, and missing data will be imputed. Missing observations will be assumed to be missing at random and imputed using multiple imputations. Censored data due to death or withdrawal for other reasons will be imputed using survival analysis.

ICERs will be estimated as cost per QALY gained for the primary and sensitivity analyses. Analysis of covariance (ANCOVA) will be used to estimate the net costs and QALYs associated with the training intervention to adjust for any differences in baseline characteristics of patients or practices. The cost-effectiveness acceptability analysis will be generated from the ANCOVA to estimate the probability that an intervention is cost-effective [93]. The cost-effectiveness acceptability analysis will be used to estimate the probability that an intervention is cost-effective using ceiling thresholds in the range £0 per QALY gained to £30000 per QALY gained, in increments of £1000. Bootstrap estimates of the ICER and net benefit statistic (mean 2.5th to 97.5th percentile), cost-effectiveness plane and cost acceptability curve will be presented [89,90].

Sensitivity analysis will be used to test the effects of assumptions and data on the ICER, and results of the cost-effectiveness acceptability analysis. These will include testing the effects of varying the discount rate used, extrapolating the results over longer timeframes, the unit cost sets used to value resources, the methods used to impute missing data; and the outcome measure used in the ICER including 1) severity of depressive symptoms (SCL-90, PHQ-9), 2) health perceptions (IPQ), 3) self-management behaviors, and 4) other measures of health status.

SPSS Statistics (IBM, version 20.0) will be used for data manipulation and descriptive analysis. Stata 12 (StataCorp, Texas 77845–4512, USA) will be used for the main statistical analyses, and imputation and estimation of net benefit statistics and cost-effectiveness acceptability analysis [93,94].

### Analysis

The method of allocation of practices to the collaborative care or control arm will be based on simple randomization (that is, 50:50 chance) for the first six practices. Minimization will be used thereafter with 0.7/0.3 probabilities. For each allocation, the balance score will be estimated based on thresholds for practice list size and deprivation, measured using the Index of Multiple Deprivation.

All analyses will be conducted on an intention-to-treat basis subject to the availability of data. After data cleaning, the preliminary analysis will investigate the pattern of missing baseline and follow-up data. The effect of the collaborative-care treatment program on depression outcomes will be estimated using a multi-level mixed-effects linear regression model, including a random effect for practices, and controlling for the following baseline covariates: patient age, gender, ethnicity, and baseline PHQ-9 score. Given that the continuous outcomes are likely to have a skewed distribution, bootstrap sampling (a method free from parametric assumptions) will be used to derive estimates of error variance for the tests of statistical significance, using 10,000 samples. Sensitivity analysis will be carried out to check the implications of different assumptions about the missing data.

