In the COINCIDE trial, the case managers will be psychological well-being practitioners (PWPs) who are graduate psychologists who provide high-volume, low-intensity psychological interventions based on a cognitive and behavioral model for patients with depression and anxiety disorders. PWPs are employed by IAPT teams, who are commissioned in each primary-care trust (PCT). IAPT was established in 2006 to improve access to routine, evidence-based, first-line treatment for adults of working age following calls from Layard [42] for a new deal for people with depression and anxiety disorders. As part of the UK government’s commitment to mainstream mental health in England and to reduce inequities between physical and mental-health services [43], the scope of IAPT will be broadened to include a standalone program for children and young adults, and the development of care models for people with LTCs, medically unexplained symptoms, and severe mental illness [44].

Training PWPs to become case managers to deliver collaborative care for people with LTCs and depression thus not only fits the strategic goals of the NHS and IAPT, but also meets the needs of the CLAHRC to identify and evaluate interventions that stand the greatest chance of implementation in routine settings. As well as being premised on strategic and pragmatic goals, the decision to train PWPs in this trial also draws on a robust evidence base that shows that the effect size of collaborative care is higher in studies in which case managers have a specific mental-health background [24].

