### Study setting and sample size

#### Recruitment of IAPT services

This study will be based in primary care across a geographical area that includes 13 PCTs in the north west of England. We will recruit IAPT services that provide low-intensity psychological therapies. All IAPT teams that fall within the catchment area of the target PCTs will be eligible for inclusion. Within each IAPT service, clinical team leaders will nominate PWPs to receive the training in the new collaborative-care model for people with depression and diabetes/CHD. The ratio of trained to untrained PWPs in each IAPT service will vary depending on the size of the team; however, it is estimated that we will need to train up to two PWPs per IAPT team to accommodate the case loads generated by the clinical trial. Furthermore, in the context of this pragmatic trial, training multiple therapists protects the trial from drop-out from PWPs, and allows for more robust assessment of therapists’ effects. Each IAPT team that is included in the trial will retain capacity to offer psychological therapy services to other groups, including patients referred from general practices that are randomized to the usual care arm.

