### Patient recruitment

#### Sample size

Based on a UK trial of collaborative care for major depressive disorder [29] we have powered this trial to detect a standardized effect size of 0.4. If each of the 30 practices (15 in each arm) recruits 15 patients at baseline (450 in total), the study will have > 80% (81.2%) power to detect this size of effect at the 5% level of significance, allowing for an intraclass correlation coefficient (ICC) of 0.06 (that was identified in a previous Phase II trial of collaborative care) and a 20% attrition rate.

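### The outcome model clusters by practice only; if trained PWPs serve more than one intervention practice, the standard error of the treatment effect may be too small, by an amount the protocol does not let a reader fix

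*Protocol article*

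**What the plan says.** The Analysis section fixes a multi-level linear model for the depression outcomes, "including a random effect for practices, and controlling for the following baseline covariates" of age, gender, ethnicity and baseline PHQ-9. No term for PWP or IAPT team appears. The error variance is to come from 10,000 bootstrap samples, and the resampling unit is not stated.

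The sample-size section likewise works with one clustering level, "allowing for an intraclass correlation coefficient (ICC) of 0.06".

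Delivery is organised at another level. Under Study design, "PWPs are employed by IAPT teams, who are commissioned in each primary-care trust (PCT"). Under Recruitment of IAPT services the area covers 13 PCTs, and "it is estimated that we will need to train up to two PWPs per IAPT team". The same section argues that "training multiple therapists protects the trial from drop-out from PWPs, and allows for more robust assessment of" therapists' effects. The Usual care section keeps trained PWPs away from control patients, so any clustering by trained PWP exists in one arm only. Practices are allocated by minimization on list size and deprivation; PCT and IAPT team are not factors.

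The article does not give the number of teams or PWPs taking part, the number of practices per PWP, or a PWP-level ICC.

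**The concern.** A PWP belongs to an IAPT team, not to a practice. If one PWP treats patients from two or more intervention practices, that PWP's better or worse results move those practices together. The shared component enters the variance of the intervention-arm mean in full. It largely cancels from the spread between practices, and that spread is what a practice-only model uses as its error. The standard error for the primary comparison can then be too small and the 5% test can reject too often.

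The bootstrap as described does not settle this: resampling whole practices would still treat practices that share a PWP as independent.

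The protocol also gives assessment of therapists' effects as a reason for training several PWPs, yet the one outcome model it sets out cannot separate them from practice effects.

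**Working it through.** **The plan's own figure.** The inputs in the Sample size section are a standardized difference of 0.4, 15 practices per arm with 15 patients apiece, a practice ICC of 0.06 and 20% loss to follow-up. For these it claims "> 80% (81.2%) power to detect this size of effect at the 5% level of significance". Completers per practice: 15 × 0.8 = 12. Design effect: 1 + 11 × 0.06 = 1.66. Effective size per arm: 180/1.66 = 108.4. Standard error: √(2/108.4) = 0.1358. A two-sided noncentral t test with 30 − 2 = 28 df gives 81.1%, which agrees with the stated 81.2%. That power rests on practice clustering alone.

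**How likely is sharing?** If each PCT has one team (an assumption; the text gives no count), 15 intervention practices in at most 13 teams force at least one team to serve two or more. Random allocation makes more sharing likely. Suppose 30 practices are spread as evenly as possible over 13 teams: four teams with 3 practices and nine with 2. The chance that an intervention practice has another intervention practice in its team is 1 − (15/29)(14/28) = 0.741 in a team of three and 14/29 = 0.483 in a team of two. The expected number is 6 × 0.741 + 9 × 0.483 = 8.8 of 15. Over 8 teams (six with 4 practices, two with 3) it is 12.7 of 15. A shared team need not mean a shared PWP.

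**Size.** From the protocol: 15 practices per arm, 12 completers each, practice ICC 0.06. Assumed: PWP ICC ρ of 0.02 or 0.05 in the intervention arm only, a team's two PWPs splitting its patients equally, intervention practices spread evenly over teams, total variance 1, covariates ignored.

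- B = [2 × 0.06 + 0.94/12 + (0.94 − ρ)/12]/15
- True variance of the effect = B + ρS, where S is the sum over PWPs of the squared share of the intervention arm. With two PWPs per team and k practices in a team, S = Σk²/450; with one PWP per team, S = Σk²/225.
- Expected variance from the practice-only model = B + ρ(½ − S)/14, with 1 in place of ½ for one PWP per team.

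Example: 5 teams of two PWPs, 3 intervention practices per team, ρ = 0.05. S = 45/450 = 0.1 and B = 0.01817. True variance = 0.01817 + 0.00500 = 0.02317, standard error 0.1522. Model variance = 0.01817 + 0.05 × 0.4/14 = 0.01960, standard error 0.1400. Ratio 1.087.

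| Intervention-arm delivery | S | True SE / model SE (ρ = 0.02; 0.05) | Simulated type I error at nominal 5% |
|---|---|---|---|
| One PWP per practice, none shared | 0.067 | 1.000; 1.000 | 5.1%; 5.1% |
| 13 teams × 2 PWPs | 0.042 | 1.005; 1.012 | 5.2%; 5.3% |
| 8 teams × 2 PWPs | 0.064 | 1.017; 1.041 | 5.4%; 5.9% |
| 5 teams × 2 PWPs | 0.100 | 1.037; 1.087 | 5.9%; 7.1% |
| 3 teams × 2 PWPs | 0.167 | 1.073; 1.170 | 6.7%; 9.1% |
| 5 teams × 1 PWP | 0.200 | 1.071; 1.158 | 6.6%; 8.8% |

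The simulations use a t test on practice means with 28 df, which matches the practice-random-intercept model at equal cluster size. Allocating practices to arms at random across teams raises the figures somewhat: about 5.5% for 13 teams × 2 at ρ = 0.03, and 10.9% for 5 teams × 1 at ρ = 0.05.

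**The case against.** The strongest reply is that the document does not establish the harm. No passage says a PWP covers several practices, and none fixes one team per PCT. Thirteen teams with up to two PWPs each could supply 26 PWPs for 15 intervention practices. Where a PWP serves one practice only, the practice effect absorbs all of the PWP variance and nothing is lost. This stands, and it makes the point conditional.

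The type I figures also assume that PWPs differ while the average effect is exactly zero. If the intervention did nothing for anyone, the extra variance in one arm would vanish and so would the inflation. Whether to generalise beyond the participating PWPs is a choice of inferential target. This stands as a caveat on the type I figures; an interval meant to apply to other PWPs still needs their variance.

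A condensed article may leave therapist terms to an analysis plan that is not shown. A reader might therefore infer that a promised therapist analysis is never made. The documents do not support that: the remark about therapists' effects is a design rationale naming no analysis, and a fuller plan may contain one. What remains is that the published model states its clustering structure explicitly, and that structure does not fit the stated delivery or that rationale.

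**Conclusion.** The concern holds in a conditional form. The stated model has a practice effect only, while delivery is by a few PWPs per IAPT team in one arm. If PWPs span practices and differ in their results, the practice-only standard error is too small. For assumed PWP ICCs of 0.02 to 0.05 and two PWPs per team, the excess of true over model standard error is about 0–2% with 13 teams and about 2–9% with 5 to 8. The larger figures need very few PWPs.

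A reader might go further and conclude that the standard error is too small, or that PWP differences are ignored. The text supports neither. The first depends on team numbers, caseloads and an ICC that are not given; the second overlooks the part that the practice effect absorbs. This is a modest weakness in a stated analysis choice, worth correcting because correction is cheap.

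**What to change.** Record the PWP for every intervention patient. The Training and supervision section already has PWPs keep a monitoring sheet per patient, so identity is available for those treated. Give a rule for patients who never see a PWP, for example attributing them to the PWP assigned at referral.

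Prespecify the Analysis model with an added PWP random effect confined to the collaborative-care arm and crossed with practice, at least as a sensitivity analysis. Report the PWP variance component and the numbers of teams, PWPs and practices per PWP. In simulation this model brought type I error to 3.9–5.3% with two PWPs per team (6.9% with 5 teams of one PWP).

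The cost is analysis wording and one recorded field. The standard error widened by about 1–3% when there was no PWP variance, and the component will be imprecise with few PWPs.

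An IAPT-team random treatment slope is not advised as a fallback. With 5 teams it leaves about 4 df, raising the critical value from 2.05 to 2.78, an interval about 36% wider (2.78/2.05 = 1.36) before any change in the standard error.
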